## Abstract

**Background:**

Chemotherapy-induced peripheral neuropathy (CIPN) is a debilitating and dose-limiting side effect of systemic cancer therapy. In many cancer survivors, CIPN persists after treatment ends and is associated with functional impairments, abnormal gait patterns, falls, and diminished quality of life. However, little is known regarding which patients are most likely to develop CIPN symptoms that impair mobility and increase fall risk, when this risk develops, or the optimal timing of early intervention efforts to mitigate the impact of CIPN on functioning and fall risk. This study will address these knowledge gaps by (1) characterizing trajectories of symptoms, functioning, and falls before, during, and after treatment in adults prescribed neurotoxic chemotherapy for cancer; and (2) determining the simplest set of predictors for identifying individuals at risk for CIPN-related functional decline and falls.

**Methods:**

We will enroll 200 participants into a prospective, observational study before initiating chemotherapy and up to 1 year after completing chemotherapy. Eligible participants are aged 40–85 years, diagnosed with stage I-III cancer, and scheduled to receive neurotoxic chemotherapy. We perform objective assessments of vibratory and touch sensation (biothesiometry, tuning fork, monofilament tests), standing and dynamic balance (quiet stance, Timed-Up-and-Go tests), and upper and lower extremity strength (handgrip dynamometry, 5-time repeated chair stand test) in the clinic at baseline, every 4–6 weeks during chemotherapy, and quarterly for 1 year post-chemotherapy. Participants wear devices that passively and continuously measure daily gait quality and physical activity for 1 week after each objective assessment and self-report symptoms (CIPN, insomnia, fatigue, dizziness, pain, cognition, anxiety, and depressive symptoms) and falls via weekly electronic surveys. We will use structural equation modeling, including growth mixture modeling, to examine patterns in trajectories of changes in symptoms, functioning, and falls associated with neurotoxic chemotherapy and then search for distinct risk profiles for CIPN.

**Discussion:**

Identifying simple, early predictors of functional decline and fall risk in adults with cancer receiving neurotoxic chemotherapy will help identify individuals who would benefit from early and targeted interventions to prevent CIPN-related falls and disability.

**Trial registration:**

This study was retrospectively registered with ClinicalTrials.gov (NCT05790538) on 3/30/2023.

## Introduction

Chemotherapy-induced peripheral neuropathy (CIPN) is a persistent cancer treatment-related side effect that negatively impacts physical functioning, falls, and quality of life [1–4]. CIPN typically affects the hands and/or feet, with numbness, tingling, pain, cold hypersensitivity, and muscle weakness among the most common sensory and motor symptoms [5, 6]. CIPN is estimated to occur in 25%-90% of patients during chemotherapy and persists in many survivors long-term [7–9]. Multiple classes of neurotoxic chemotherapy drugs are associated with CIPN, including taxanes, platinum derivatives, and vinca alkaloids [10]. The etiology and natural history of CIPN are heterogeneous across classes of neurotoxic chemotherapeutic agents [11, 12]. Not all patients receiving the same neurotoxic treatment regimen will develop CIPN, but for those who do, symptom severity and recovery after treatment vary widely [13].

Cancer survivors with CIPN have worse physical functioning (e.g., mobility), more self-reported disability, and significantly higher fall rates than asymptomatic survivors [4, 7, 14]. In a cross-sectional study of breast cancer survivors approximately 6 years post diagnosis, distinct patterns of worsening objective and patient-reported physical function, disability, and fall risk were associated with increasing CIPN severity [4]. Most studies reporting mobility impairments due to CIPN have multiple limitations: cross-sectional design, reliance on complex measures that are impractical to capture in a clinic setting, and lack of power to capture falls. Moreover, these studies do not examine heterogeneity across patients, which may be central to identifying patients at greatest risk for poor outcomes [4, 15, 16]. Longitudinal studies reporting trajectories of CIPN symptoms and mobility deficits have been conducted, but none have linked mobility impairments to falls or the onset of disability [17, 18]. Additionally, it remains unknown when CIPN symptoms become severe enough to impair functioning and increase fall risk.

Until a simple system for identifying when and which patients are at risk for CIPN-related mobility deficits can be incorporated into the clinical workflow and used to target early intervention strategies, falls and disability from CIPN will likely remain underrecognized and undertreated. A critical first step toward identifying simple, early predictors of functional decline and developing fall risk is to characterize the natural trajectories of symptoms, functioning, and falls across the in-treatment and recovery phases of cancer care. Thus, we are conducting a longitudinal observational study examining patterns of CIPN symptom development, disability onset, and falls in adults with cancer before, during, and after neurotoxic chemotherapy. We simultaneously track symptoms, functioning, and falls through patient-reported symptoms, disability, and physical functioning; objective physical performance measures; and continuous passive monitoring of physical activity and mobility during chemotherapy and 1 year into recovery.

## Methods

### Study aims and hypotheses

Our study aims and hypotheses are three-fold: (1) Characterize the variability in trajectories of CIPN symptoms and physical functioning in patients across treatment and 1 year of recovery. We hypothesize that there will be significant congruence between worsening CIPN symptoms and declining physical activity, mobility, and self-reported physical functioning and disability; (2) Identify 2 or more distinct trajectories of change in symptoms and functioning associated with significant differences in fall rates. We hypothesize that we can identify 2 or more distinct trajectories of CIPN and physical functioning associated with falls; and (3) Identify the simplest set of predictors that identify patients at risk for CIPN-related functional decline and falls. We hypothesize that some combination of patient characteristics (e.g., age, sex, comorbidities, body mass index), chemotherapy features (e.g., chemotherapy drug class, number of chemotherapy cycles, cumulative chemotherapy dose), and mobility measures (gait, balance) will predict distinct trajectories of change in CIPN symptoms and physical functioning [9, 19, 20].

### Study design and setting

This single-center, prospective, observational study is being conducted at the Knight Cancer Institute at Oregon Health & Science University (OHSU). Participants are recruited from the main OHSU Knight Cancer Institute clinic and 5 OHSU Knight Cancer Institute community hematology-oncology clinics around the Portland metropolitan area. The study was approved by the OHSU Institutional Review Board (#21969) and registered with ClinicalTrials.gov (NCT05790538).

### Study participants

The target population is adults with cancer scheduled to receive neurotoxic chemotherapy with curative intent. To be eligible to participate, participants must meet the following eligibility criteria:Age 40–85 years on the date of enrollment. We chose this age range because the side effects and symptoms from chemotherapy may differ between young, middle-aged, and advanced-aged patients, and the subsequent impact on mobility may be similarly diverse. We exclude adolescent and young adult patients (15–39 years old) who may be less vulnerable to falls and disability at a young age and adults over 85 years to limit mobility/falls associated with advanced age and multi-morbidities. The age range of patients in the study is broad enough to examine the influence of age on study outcomes.Diagnosed with stage I-III cancer, or stage IV cancer considered curable, other than cancers or metastases in the brain or spinal cord.Patients scheduled to receive neurotoxic chemotherapy, including taxane derivatives, platinum complexes, and/or vinca alkaloids.Patients without prior receipt of neurotoxic chemotherapy.Patients without cognitive difficulties that preclude answering survey questions, participating in performance tests, or giving informed consent as determined by the referring provider.Patients must be free of a medical condition, movement or neurological disorder, or medication use that contraindicates participation in mobility testing and/or confounds the ability to detect treatment-related changes in balance and mobility. Specific medical conditions include, but are not limited to, severe muscular dystrophy, severe spasticity, epilepsy, seizures, Alzheimer’s disease, and dementia; specific physical conditions include a severe balance disorder (e.g., from late-stage Parkinson’s disease or stroke), inability to ambulate (use of an assistive device is permitted), inability to stand for 3 min, or severe hearing or vision problems.

### Participant recruitment and retention

We plan to enroll 200 participants. Patients are identified through chart reviews, tumor boards, and direct referrals from oncology clinicians. With the clinician’s permission, a research coordinator contacts the patient by phone to explain the study and screen for eligibility. Written informed consent is obtained electronically via the OHSU electronic data management system (REDCap) before or at the first study visit. For patients we cannot contact prior to their first chemotherapy infusion, or who express that they are too overwhelmed for a research visit at their first infusion, we offer to delay study enrollment until the second chemotherapy cycle. Patients are not enrolled after their second chemotherapy cycle because important information about early changes in symptoms and function can no longer be obtained.

We use several strategies to retain participants in the study. One research assistant is assigned to each participant throughout the study to establish a trusting relationship between each participant and a research team member. We minimize participant burden by using home-based data collection (online surveys and passive monitoring devices) and by conducting testing visits in the clinic just prior to regularly scheduled oncology appointments. If participants do not have a scheduled post-treatment clinic visit within the desired time frame, they are asked to schedule a separate research visit at the Knight Cancer Institute. Participants are remunerated for each study visit ($25 for research visits that coincide with clinic visits or $50 for separate post-treatment research visits). Travel compensation is provided for participants who live > 30 miles from OHSU to attend separate post-treatment research visits.

### Procedures

Data collection uses the following methods: (a) clinic-based assessments of vibration and tactile sensation for CIPN and performance tests of physical functioning, (b) home-based assessments of symptoms and functioning using web-based surveys and wearable devices to monitor daily physical activity and mobility, and (c) data on cancer history, medications, and chemotherapy regimens abstracted from the electronic health record (EHR) (Fig. 1).

**Fig. 1 Fig1:**
[figure not shown]
Data collection timeline. Data are collected in the clinic and at home. Participants complete objective neuropathy and performance assessments at chemotherapy infusion visits (C1, C2, C3…) every 4–6 weeks and at follow up oncology visits (R1-R4) every 3 months during the first year of recovery. At home, participants wear wearable devices for 4–7 days following each clinic assessment and complete weekly electronic surveys throughout the study

Clinic-based data collection occurs during chemotherapy according to each patient’s treatment schedule and post-chemotherapy at quarterly intervals for 1 year. The baseline clinic assessment occurs before the first or second chemotherapy cycle, and then assessments are repeated every 4–6 weeks (coincident with the treatment schedule) until the final chemotherapy infusion. CIPN and performance measures are taken during clinic visits before chemotherapy administration. Post-chemotherapy (i.e., recovery), clinic assessments are performed with routine follow-up care at approximately 3-, 6-, 9-, and 12-months post-chemotherapy.

Home-based data collection consists of web-based surveys and wearable devices. Survey invitations are sent via SMS or email according to individual preference. Brief symptom and fall surveys are administered weekly during the study. More detailed physical functioning and disability surveys are administered at time points coinciding with clinic assessments. At the end of each clinic assessment, participants receive wearable devices that measure physical activity and gait quality passively and unobtrusively in their homes. Participants are asked to wear the devices for at least 4 of the next 7 days and at least 6–8 h per day during waking hours. After 7 days, participants mail the devices back to OHSU in pre-paid, pre-addressed shipping boxes or return them to study staff at their next clinic assessment.

### Outcome measures

#### Symptoms

##### Objective CIPN measures

Loss of perceived sensation is a widely accepted clinical measure to screen for CIPN [21]. We perform 3 tests of loss of perceived sensation.*Tuning fork test*: Vibratory sensation is measured by placing a 128 Hz vibrating tuning fork (US Neurologicals, LLC, Poulsbo, WA) proximal to the nail bed on the right dorsal hallux and recording the time that elapses before the participant indicates they can no longer detect vibration [22]. Three trials of the test are conducted and then averaged.*Monofilament test*: The tester records the number of times an individual detects 4 brief applications (~ 1 s) of a 10-g monofilament (Medical Monofilament, Plymouth, MA) on the sole of each foot, for a total of 8 sites [22].*Biothesiometry*: The lowest amplitude of vibration that an individual can detect, or vibration perception threshold (VPT), is assessed using a biothesiometer (Biothesiometer USA, Avon Lake, OH) [23]. A handheld device that varies vibration amplitude at a constant frequency is placed proximal to the nail bed on the right dorsal hallux. The VPT is measured by slowly increasing the amplitude from 0 V until the individual indicates that they detect vibration in their toe. Two trials are performed and averaged to generate the VPT. Biothesiometry is only performed at the final chemotherapy infusion and at all post-chemotherapy assessments.

##### **Patient-**reported** CIPN**

Patient-reported CIPN is assessed using the Patient-Reported Outcomes version of the Common Terminology Criteria for Adverse Events v1.0 (PRO-CTCAE™: https://healthcaredelivery.cancer.gov/pro-ctcae/) reporting tool and the Functional Assessment of Cancer Therapy – Gynecologic Oncology Group Neurotoxicity 13-item questionnaire (FACT-GOG-Ntx-13) [24–27]. Two PRO-CTCAE™ items are administered weekly, asking the patient to report whether they experienced numbness or tingling in the hands or feet and how much the symptom interfered in their daily life during the last 7 days. We also administer the 13-item neuropathy subscale of the FACT-GOG-Ntx-13 which assesses the presence, severity, and interference of neuropathy symptoms in patients receiving neurotoxic chemotherapy. The scale ranges from 0–52, with lower scores indicating worse quality of life due to neuropathy. Both surveys are sent weekly for the duration of the study.

##### Other symptoms

Patient-reported symptoms (dizziness, cognitive function, pain, insomnia, fatigue, anxiety, and depressive symptoms) are assessed with PRO-CTCAE™ reporting tool items that assess the severity, frequency, and interference of each symptom in daily life during the previous 7 days [25]. Symptom surveys are sent weekly for the duration of the study.

### Physical functioning

#### Objective performance measures

##### Upper extremity strength

Upper extremity strength is measured via hand grip dynamometry, an approach used in standard neuropathy assessments to determine whether neuropathy involves motor neurons [21, 28, 29]. Grip strength in the dominant hand is measured with a handgrip dynamometer (Creative Health Products, Ann Arbor, MI). Participants stand with their feet shoulder-width apart and arms hanging loosely at their sides. Participants are first cued to inhale and then prompted to exhale while squeezing the dynamometer as hard as they can, and the maximum force (in kg) is recorded. The procedure is repeated 2 more times for a total of 3 trials, which are then averaged.

##### Lower extremity function

Lower extremity function is measured by a timed chair stand test, measured as seconds required to rise from a sitting position in a chair to a full stand 5 times in a row [30–32]. Chair stand times > 12 s have been shown to predict a 2.4-fold increased risk of falls in older adults [33].

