##### Static balance

Static balance is assessed by a postural sway test that measures how well a person can maintain their balance during quiet standing. Increased sway indicates poor balance control, is associated with an increased risk of falls, and is greater in populations with neurologic impairment [34, 35]. Postural sway is measured with a Mobility Lab Opal sensor and software (APDM Wearable Technologies, Clario, Portland, OR). The wireless, Opal inertial sensor placed on the lumbar region captures multiple postural sway variables, including total sway area (m^2^/s^4^) and mean sway velocity (m/s). Participants are asked to stand as still as possible with feet together and hands on hips for 30 s. The test is first conducted with eyes open and then repeated with eyes closed.

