##### Dynamic balance

Dynamic balance is measured by the Timed-Up-and-Go (TUG) test, a widely accepted clinical measure of dynamic balance in older adults and clinical populations [36]. The TUG test evaluates the time in seconds that it takes an individual to rise from a chair, walk 3 m at their usual pace, turn around, and return to a seated position in the chair. The procedure is repeated for a total of 2 averaged trials to calculate TUG time. Slower TUG times are associated with an increased risk of falls and disability and have been observed in taxane-treated breast cancer survivors relative to healthy controls [31, 37–39].

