#### Handling missing data

The mixed-effects growth models will be estimated with maximum likelihood, which utilizes all available outcome data for each participant without removing participants due to missingness [57]. For the GMM stage, full-information maximum likelihood (FIML) estimation will be used to handle data that is missing completely at random (MCAR) or missing at random (MAR). For data that are MAR, variables related to the missingness will be included using the auxiliary command in Mplus (i.e., to allow unbiased parameter estimation under MAR) while not including them in the data analysis model [58]. These approaches will allow the analysis of the proposed aims in the case of patient withdrawal, maximizing statistical precision and power.

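### A patient who becomes unable to complete the chair stand, TUG or stance has no value on the analysed scale, and handling missing data only under MCAR/MAR understates that patient's decline

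*Protocol article*

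**What the plan says.** All references are to the protocol article.

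- **Lower extremity function:** the chair stand is "measured as seconds required to rise from a sitting position in a chair to a full stand 5 times in a row".
- **Dynamic balance:** TUG is in seconds. "The procedure is repeated for a total of 2 averaged trials to calculate TUG time".
- **Static balance:** "Participants are asked to stand as still as possible with feet together and hands on hips for 30 s". There are two conditions, the second without vision.
- **Specific analysis plan:** each symptom and functioning outcome gets its own mixed-effects model in lme4. The individual intercepts and slopes are correlated (Hypothesis 1.1) and then entered into the latent class model (Hypothesis 1.2).
- **Handling missing data:** the mixed models use maximum likelihood, which "utilizes all available outcome data for each participant without removing participants due to missingness". At the class stage, "full-information maximum likelihood (FIML) estimation will be used to handle data that is missing completely at random (MCAR) or missing at random (MAR". Under MAR, "variables related to the missingness will be included using the auxiliary command in Mplus". The only cause of missing data that the section names is withdrawal.
- **Study participants:** exclusions include a severe balance disorder, conditions that rule out mobility testing, being unable to stand for 3 minutes, and "inability to ambulate (use of an assistive device is permitted").

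None of these sections gives a value, censoring rule or category for a patient who cannot complete a test.

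**The concern.** A time to completion does not exist for a patient who cannot complete. The sensory tests differ: on the tuning fork and the monofilament, complete loss of sensation scores 0 s or 0 of 8, so the worst state has a place on the scale. For the chair stand, TUG and stance it has none.

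If neuropathy progresses until a patient can no longer rise five times, or hold the stance with eyes closed, the missing value is missing because it would have been bad. MAR is not credible for that gap. The patients concerned are those the study sets out to find: people whose function declines toward disability and falls. If their slopes are understated, the declining class looks milder and its link with falls may weaken.

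**Working it through.** **1. The plan's own figure.** No stated figure bears on inability. The stated detectable difference reproduces: n per class = 2 × (1.960 + 0.842)² / 0.40² = 2 × 7.85 / 0.16 = 98.1, rounded up to 99. That is 198 in total against 200. It does not depend on how missing tests are treated.

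**2. The route of a blank through the stated analysis.**
- Stage 1 fits one outcome at a time. Disability, quality-of-life and fall data therefore do not inform the chair-stand slope. Only the patient's earlier chair stands do.
- With fewer and milder observations, the individual slope shrinks toward the population mean.
- FIML and the auxiliary variables act at stage 2, in Mplus. There the patient already has a slope, not a missing value, so they have nothing to repair.
- Hypothesis 1.1 correlates the slopes of every functioning outcome. It is affected whichever six function measures enter the class model.

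**3. Size under assumed inputs.** The documents give none of these: 200 patients; 8 visits; baseline 10 s (SD 2); residual SD 1; 20% decline at 1.0 s per visit (SD 0.3), the rest at 0.1 (SD 0.15). Once a post-baseline time would exceed a threshold, the test is missing from then on. The model has a random intercept and slope and is fitted by maximum likelihood. With nothing missing, the declining group's mean estimated slope is 0.900.

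| Threshold | Cohort becoming unable | Decliners' visits missing | Decliners' slope | Fall from 0.900 | Unable patients' slope, full data | Same, blank = missing | Loss |
|---|---|---|---|---|---|---|---|
| 20 s | 4% | 4% | 0.875 | 3% | 1.25 | 1.05 | 16% |
| 18 s | 8% | 12% | 0.784 | 13% | 1.11 | 0.84 | 24% |
| 16 s | 16% | 24% | 0.613 | 32% | 0.91 | 0.54 | 41% |

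Loss = 1 − (blank / full data), for example 1 − 1.05/1.25 = 0.16. The decliners' columns come from 30 runs per setting. The last three columns come from a separate set of 20 runs, some with convergence warnings. The first set gave 1.05, 0.82 and 0.55 for the blank column, so the two agree. Against true slopes the loss is 1 − 1.05/1.288 = 0.185 up to 1 − 0.547/0.957 = 0.428, but that includes the ordinary shrinkage of any mixed model.

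At 16 s, patients who became unable looked milder than the average decliner (0.54 against 0.60). At about 4% inability, the AUC separating decliners from others was unchanged at 0.987, and unable patients moved only from about the 96th to the 94th percentile of slope.

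**4. An upper bound on another scale.** Assume 30% decline, and completers among them go from 0.42 to 0.33 stands/s (5/0.42 = 11.9 s; 5/0.33 = 15.2 s). Assume 2% to 5% of the cohort become unable, all of them decliners: 2/30 = 6.7%, 5/30 = 16.7%. With inability scored 0:
- 0.33 × 0.933 = 0.308, a fall of 0.112 against 0.09 in completers. Hidden share 0.022/0.112 = 20%.
- 0.33 × 0.833 = 0.275, a fall of 0.145. Hidden share 0.055/0.145 = 38%.

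This ignores what the mixed model recovers from earlier visits, and it takes the zero score as the truth.

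**5. Candidate remedies in the same simulation.**
- Entering the threshold itself as the score barely helps: 0.613 to 0.673 at 16 s.
- On a rate scale with blanks left missing, unable patients looked milder than decliners overall (−0.21 against −0.26 at 20 s). Scoring 0 made them the steepest (−0.46 against −0.31).
- The zero-scored rate separated the classes worse than seconds at 4% to 8% inability (AUC 0.96–0.97 against 0.98–0.99) and better only near 16%. The simulated decline is linear in seconds, which favours the seconds scale.

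**The case against.** The strongest objection is that the point leans on silence. The article never says that inability is left blank, and a condensed article may leave scoring of failed tests to a manual or the full protocol. A sensor may also capture part of a stance. This stands in part: if a scoring rule exists elsewhere, the point narrows to stating it. But a manual that merely records inability would not change the stated analysis, which uses seconds and assumes MCAR or MAR.

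Three stronger readings are tempting, and the documents do not support them.

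- **That the worst patients drop out.** They do not. Earlier visits are kept, and grip strength, wearable data, patient-reported function, disability and weekly falls continue. The effect is a shrunken slope.
- **That patients unable to do the tests can enter freely.** The eligibility criteria go well beyond walking and standing for 3 minutes and largely screen out inability at baseline. The concern is with inability that develops later, and it is weaker for TUG than for the chair stand or the eyes-closed stance.
- **That a zero-scored rate must replace seconds.** Step 5 shows that it can separate classes less well. A cluster of zeros could itself create a class. Six metres divided by TUG time is not walking speed, because the time includes rising, turning and sitting. Analysing sway from completed trials alone would keep the same gap.

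**Conclusion.** The point holds in a limited form. As the analysis is stated, a test missing because the patient has become unable is informative. It shrinks that patient's slope at stage 1, and nothing at stage 2 restores it. Under the assumed inputs, the slopes of patients who became unable were understated by 16% to 41% as inability rose from 4% to 16% of the cohort, and the declining group's mean slope by 3% to 32%.

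The rate of inability is not given, and the size depends on it. If inability is rare, class separation is hardly affected. The 20% to 38% in step 4 is an upper bound that rests on its assumptions, not an estimate. The change is worth making because the reason for a blank is cheap to record at the visit and hard to reconstruct later.

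**What to change.** 1. At each visit, record whether a missing test was attempted or judged physically impossible, or was not done for another reason. Leave only the second kind to the MAR assumption.
2. Pre-state an analysis that counts physical inability as a poor outcome, at least as a sensitivity analysis to the seconds-scale slopes and class assignments:
   - chair stand and TUG: a right-censored time, or reciprocal time with 0 for unable;
   - stance: seconds held, analysed alongside sway.
3. Check that a cluster of zeros does not itself produce a latent class.
4. If a rule for inability already exists in the full protocol or testing manual, state it and say how it enters the mixed models.

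**Cost.** One form field, which may be unavailable for visits already made because the study is under way; one additional analysis; and, if reciprocal time is used, a less familiar scale that can be back-transformed for reporting. Inability from causes other than neuropathy would also count as decline, which should be said when results are interpreted.
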